### Settings and study participants

Prospective participants will be recruited from 38 aged care facilities in urban and rural Victoria, Australia. Before enrolment or study assessments being performed, prospective participants will be asked to sign a written consent form. Residential care staff will identify participants who are cognitively able to give informed consent. Participants who consent to participate in the study will be screened for study eligibility by a research assistant.

The inclusion criteria are:Presenting distance < 6/12 (0.30; Logarithm of the Minimum Angle of Resolution-LogMAR) and/or near vision ≤ N8 (1.00 M) assessed uniocularly and binocularly using the Bailey-Lovie LogMAR [16] charts;Able to speak English;Moderate cognitive functioning or better as assessed by the Psychogeriatric Assessment Scale (PAS) [17] (score ≤ 15);Ability to undergo VA testing and provide reliable results.

The exclusion criteria are:Residents in respite care (short-term stay);Severe cognitive impairment (score of ≥ 16 on the PAS);Non-English speaking;Inability to be tested for vision;Contraindication(s) as indicated by the general practitioner responsible for the resident’s care.

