### Randomization

An independent statistician will perform the randomization sequence generation using a computer-generated list. For logistical reasons and to minimize confounding effects, stratified cluster randomization designs will be used to randomize participants by residential aged care facility (stratified by size and region) to the intervention (ROC) or control (usual care) arm. Participants in the same aged care facility will all be assigned to the same study arm. The allocation sequence will be concealed from the research assistants enrolling and assessing participants. Residential care facility staff, the research study coordinator, and the eye health professionals delivering ROC will not be masked to the group allocation as this is impractical.

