#### Person-centered outcomes (secondary)

Mobility will be assessed using the Aged Care Funding Instrument (ACFI) [20] module 2 developed by the Department of Health and Ageing. This component of the ACFI relates to the participant’s usual day-to-day assessed care needs with regard to mobility. Mean mobility scores will be compared between groups. ACFI data will be collected regularly by residential care facility staff.

Vision-specific QoL will be measured using the Impact of Vision Impairment for Residential Care (IVI-RC). The IVI-RC is a 28-item questionnaire developed to measure the impact of vision impairment on activity limitation and emotional wellbeing, and has been adapted specifically to the aged care setting by the study team from the original 28-item IVI questionnaire [21, 22].

Depressive symptoms will be determined using the Cornell Scale for Depression in Dementia (CSDD) [23]. This measure was chosen due to its suitability for use with individuals with moderate cognitive functioning. The interviews focus on depressive symptoms and signs occurring during the week before the interview. The final ratings of the CSDD represent the rater’s clinical impression. Each item is rated for severity on a scale of 0–2 (0 = absent, 1 = mild or intermittent, 2 = severe). The item scores are added together. Scores of 0–8, 9–13, 14–18, and 19–38 indicate no or minimal, mild, moderate, and major depressive symptoms [24].

Regarding falls rate, residential care settings have an incident reporting system (which varies from paper based to computerized systems) where any incident including falls will be recorded. Falls data will be retrieved from incident reporting systems in the participating residential care facilities and the proportion of falls will be compared between groups.

Health-related QoL will be assessed using the five-dimension EuroQoL (EQ-5D-3L) [25], a descriptive system that covers five dimensions (Mobility, Self-care, Usual Activities, Pain/Discomfort, and Anxiety/Depression). The EQ-5D-3L raw data can be converted to utilities, which will be used for our economic analyses.

With regard to utilization of visual devices (distance and near vision glasses; low vision aids), at the two- and six-month follow-up visits, participants in the intervention arm who have been prescribed spectacles or low vision aids, will be asked to self-report on how often the device has been used during the week, for how long it was used, and for what tasks.

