### Statistical analysis

The primary and secondary outcomes will be assessed using an intention-to-treat analysis applied to individual participants and repeated using the per-protocol sample (only participants who complete the clinical trial including the second assessment). To compare the effectiveness of ROC with usual care, presenting and best corrected near and distance VA (primary outcome) at the two- and six-month follow-ups will be analyzed and the differences from baseline VA will be used to investigate changes. The near and distance VA change is expected to be normally distributed and analysis of covariance will be used to compare the difference, adjusting for baseline values. Effect sizes for both groups will be calculated using Cohen’s d coefficient [27]. To determine the effectiveness of ROC on secondary outcomes, a Multivariable General Linear Model will be used to compare differences at two and six months from baseline on the IVI-RC, EQ-5D-3L and CSDD. If the EQ-5D-3L data are skewed, a multivariable quantile regression model will be used. Falls data will be compared across intervention and usual care groups at six months using a negative binomial regression if the data are over-dispersed. Changes in mobility will be analyzed using Mann–Whitney U tests. The difference in utilization of distance and near vision glasses and low vision aids between the treatment groups will be compared using the Chi-squared test and the utilization time will be compared using Student’s t-test or non-parametric test if appropriate. A multi-level model with a random intercept parameter will be utilized to account for within cluster correlations. All analyses will be performed using STATA version 15 (StataCorp. 2017. Stata Statistical Software: Release 15. StataCorp LLC, College Station, TX, USA).

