### Missing data

The differences between the intervention and usual care groups in the proportion and reason of participant withdrawal will be compared using the Chi-squared test. The multiple imputations method using chained equations (MICE) will be used to handle missing data.

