### Cost-effectiveness analysis

We will perform an incremental cost-effectiveness analysis from the payer perspective. Direct intervention costs (labor, material and supplies, and contracted services costs) associated with delivering the intervention over the one-year period will be collected and follow a cost collection approach described elsewhere [29]. The incremental costs of the intervention will need to account for any vision services received by the usual care group and any differences in costs for non-vision related services that may be an indirect result of the intervention. Information will be collected for any participants who fall or are hospitalized, transferred to high care or die. Aggregating these costs over the six-month period and adding them to the direct costs of the ROC intervention group, will allow the total medical costs for the intervention and the usual group to be quantified. The incremental cost-effectiveness ratio (ICER) will be calculated using the estimated mean difference in effect (EQ-5D-3L) and the estimated mean difference in costs between the intervention and the control groups. The ICER indicates the average incremental cost to gain one additional quality-adjusted life year (QALY). Cost data are likely to be skewed. Therefore, using non-parametric bootstrapping, 1000 replicates [30] will be generated to estimate the 95% confidence intervals around the ICER. A cost-effectiveness acceptability curve (CEAC) [31] will be used to show the probability that the intervention is cost-effective for a range of monetary values that a decision maker might be willing to pay for a unit change in QALYs. Cost-effectiveness will initially be quantified assuming that QALYs are only sustained for one year, but an assessment will also be made based on the assumption that they continue to accrue each year for the expected remaining life years in the study sample. Additional one-way (and n-way) deterministic sensitivity analyses will be performed to examine the effect of changing one (or n) of the model parameters.

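### The tests named for mobility, device use and withdrawal treat residents as independent although facilities are randomized, and cannot be followed together with the protocol's general random-intercept sentence

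*Protocol article*

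**What the plan says.** Randomization is by facility, stratified by size and region: "Participants in the same aged care facility will all be assigned to the same study arm". Settings and study participants gives the number of clusters: "Prospective participants will be recruited from 38 aged care facilities in urban and rural Victoria, Australia". Sample size assumes a within-facility ICC of 0.05.

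The Statistical analysis section of the protocol article applies the analysis to individual participants and names a method for each outcome. For mobility: "Changes in mobility will be analyzed using Mann–Whitney U tests". For glasses and low vision aids, the difference in use between groups "will be compared using the Chi-squared test and the utilization time will be compared using" Student's t-test or a non-parametric alternative. Near the end of the section comes one general sentence: "A multi-level model with a random intercept parameter will be utilized to account for within cluster correlations". It is tied to no outcome and does not say that it replaces any test named before it.

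Under Missing data, differences between the arms "in the proportion and reason of participant withdrawal will be compared using the Chi-squared test".

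Person-centered outcomes (secondary) describes the mobility comparison differently: "Mean mobility scores will be compared between groups".

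**The concern.** In a cluster randomized trial, residents of one facility share staff, routines and local services, so their outcomes tend to be correlated. A standard Mann–Whitney, Chi-squared or t-test takes its standard error from the number of residents and ignores that correlation. Part of the ordinary variation between facilities is then read as a treatment effect: p-values are too small and, where an interval is reported, it is too narrow.

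The protocol recognizes clustering in its sample size and in the general random-intercept sentence. The difficulty is that it also fixes tests that do not accommodate it. An analyst has to drop either the named tests or the general sentence, and the document does not say which. That leaves the choice open until the data are in hand. For mobility there is a second conflict: one section compares means and another specifies a rank test on changes.

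**Working it through.** **Inputs from the protocol article**
- 38 facilities, allocated 1:1, so about 19 per arm (Settings and study participants; Abstract).
- ICC 0.05, effect size about 0.65, significance level 0.05, 80% power, 50 patients per facility in the inflation factor, 10% non-compliance, 25% loss, 395 enrolled (Sample size).

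**The plan's own figure**
- An effect of 0.65 SD, two-sided 0.05 and 80% power give 38 per arm, 76 in total.
- Inflation factor: 1 + (50 − 1) × 0.05 = 3.45, stated as 3.5. Then 76 × 3.5 = 266.
- 266 / (0.90 × 0.75) = 394.1, rounded up to 395. The stated total reproduces.

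**Residents per facility as the trial is sized**
- At enrolment: 395 / 38 = 10.4.
- After 25% loss: 395 × 0.75 / 38 = 7.8.

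**Actual type I error if clustering is ignored**

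The design effect is DE = 1 + (m − 1) × ICC. A test that omits it has a standard error too small by a factor √DE, so its true two-sided error is 2 × (1 − Φ(1.96 / √DE)).

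| Residents per facility (m) | ICC | DE | √DE | Actual type I error |
|---|---|---|---|---|
| 10.4 | 0.05 | 1.47 | 1.21 | 10.6% |
| 7.8 | 0.05 | 1.34 | 1.16 | 9.0% |
| 10.4 | 0.01 | 1.09 | 1.05 | 6.1% |
| 7.8 | 0.01 | 1.07 | 1.03 | 5.8% |

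The 0.05 rows use the protocol's general ICC. The 0.01 rows are an assumed lower value, shown because the protocol gives no ICC for mobility, device use or withdrawal.

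**Check by simulation**

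Normal outcomes, 19 facilities per arm, equal facility sizes, no true effect, ICC 0.05, 6,000 runs per setting. The Chi-squared test was applied to the same outcome cut at a threshold.

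| Test | 8 per facility | 10 per facility |
|---|---|---|
| Mann–Whitney | 9.1% | 10.6% |
| t-test on residents | 9.4% | 10.7% |
| Chi-squared | 7.7% | 8.7% |
| t-test on facility means | 5.1% | 5.3% |

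The formula and the simulation agree for Mann–Whitney and the t-test. The Chi-squared figures are lower because cutting a continuous outcome weakens its within-facility correlation. Analysing facility means restores the nominal rate.

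**Can the general sentence be combined with the named methods?**
- Analysis of covariance (visual acuity), general linear model (IVI-RC, EQ-5D-3L, CSDD) and negative binomial regression (falls): yes, a random intercept can be added to each.
- t-test (use time): only by recasting it as a mixed linear model, which is no longer the named test.
- Mann–Whitney (mobility) and Chi-squared (device use, withdrawal): no. Neither has a parameter to which a random intercept could be attached.

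**The case against.** The best reply is that the random-intercept sentence is unrestricted, comes after the named tests and can fairly be read as governing all of them, with the model for each outcome left to an analysis plan that is not shown. A t-test has a direct mixed linear counterpart, and a two-group comparison of proportions has a mixed logistic one. This stands in part: the authors evidently meant to account for clustering, and the inflated error arises only if the tests are run as written. It does not remove the point. The text does not omit the methods; it names specific ones. An analysis plan that followed those names would carry the problem, and one that corrected them would depart from the protocol.

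The size can also be challenged. Mobility is analysed as change, so stable differences in how facilities score it may largely cancel, and stratification by size and region may reduce the inflation further. Both are fair, and with no outcome-specific ICC available the 9 to 11% is conditional on 0.05. Withdrawal is a descriptive check rather than an efficacy comparison.

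For device use the objection goes further. Person-centered outcomes (secondary) says that use is asked only of intervention-arm participants who were prescribed a device. On that text there are no control data to compare, so the error rates above do not apply unless collection is extended.

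A reader might infer three stronger things that the document does not support:
- **That the cost-effectiveness bootstrap ignores clustering.** The article says only "using non-parametric bootstrapping, 1000 replicates" and does not give the resampling unit. Resampling whole facilities is also non-parametric bootstrapping.
- **That the type I error could reach 29%.** That needs the 50 residents per facility of the inflation factor (DE 3.45). Fifty in each of 38 facilities would be 1,900 residents, against 395 planned.
- **That the ICC for these outcomes is well above 0.05.** The document gives no such value.

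**Conclusion.** The point holds as an internal conflict within the protocol article. For mobility, device use and withdrawal, the named tests and the general clustering sentence cannot both be carried out, and run as named the tests do not fit a facility-randomized design. For use time, following the clustering sentence means replacing the named t-test. Mobility is the clearest case: it is a secondary outcome planned for comparison between arms, its rank test cannot take a random intercept, and its two descriptions disagree.

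The consequence, at the protocol's ICC of 0.05 and the cluster sizes it implies, is roughly a doubling of the nominal 5% false-positive rate for Mann–Whitney and the t-test, and somewhat less for Chi-squared. It shrinks to about one percentage point if the ICC is 0.01. The effect on interval width bears chiefly on the t-test, since the other two mainly give p-values.

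A reader might conclude that the trial's main analyses ignore clustering. That does not follow: the main models for visual acuity, IVI-RC, EQ-5D-3L, CSDD and falls accept a random intercept, and the general sentence can reasonably be read as covering them. The quantile-regression fallback for EQ-5D-3L was not assessed here. Because only secondary and descriptive outcomes are affected, this should be fixed, but it is not a condition for the primary conclusion to stand.

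**What to change.** - **Mobility:** replace the Mann–Whitney test with a linear or ordinal model that has a facility random intercept and adjusts for baseline, or with an analysis of facility-level summaries. Use small-sample degrees of freedom suited to 38 facilities (38 − 2 = 36 for a simple comparison of facility means). Make Person-centered outcomes (secondary) and Statistical analysis describe the same comparison.
- **Withdrawal:** replace the Chi-squared test with a mixed logistic model or GEE.
- **Device use and use time:** specify a mixed logistic and a mixed linear model only if these data will also be collected in the usual care arm. Otherwise report them descriptively for the intervention arm and delete the between-group tests.
- **General sentence:** state which outcomes the random-intercept model covers and that it replaces the independent-sample tests.
- **Clarification only:** state that the cost-effectiveness bootstrap resamples whole facilities within arm.

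The cost is wording in the protocol and analysis plan. Apart from device-use data in the usual care arm, if that comparison is kept, no design change or new data are needed. Intervals will be wider than under the named tests, by a factor of about 1.16 to 1.21 at ICC 0.05 and less if the ICC is smaller.

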To date, no study has evaluated the impact of providing comprehensive eye care services to individuals with a broad spectrum of ophthalmic conditions and residing in aged care facilities. Therefore, we will implement a prospective, customized, multicentered, and cluster randomized controlled trial (RCT) to evaluate the clinical, person-centered, and cost-effectiveness of a new model of eye care. We will compare the effectiveness of Residential Ocular Care (ROC) with usual care on improving presenting and best corrected near and distance vision (primary outcome) at the two- and six-month follow-up visits. Secondary outcomes will assess the effectiveness of ROC on improving vision-specific QoL, daily functioning, health-related QoL, depressive symptoms, rate of falls, and eye care utilization, compared to the usual care group at the two- and six-month visits, after baseline, and quantify the cost-effectiveness of ROC at six months after baseline.

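### Device use is to be tested between arms, but the article describes collecting it only from ROC participants who were prescribed a device

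*Protocol article*

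**What the plan says.** Under Statistical analysis the article plans a two-arm test: "The difference in utilization of distance and near vision glasses and low vision aids between the treatment groups will be compared", by Chi-squared test. Time in use is to be compared by Student's t-test or a non-parametric alternative. The same section says that primary and secondary outcomes are analysed by intention to treat.

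Under Person-centered outcomes (secondary), the respondents at the two- and six-month visits are defined more narrowly: "participants in the intervention arm who have been prescribed spectacles or low vision aids, will be asked to self-report". They report "how often the device has been used during the week, for how long it was used, and for what tasks". No matching question is described for usual care, or for ROC participants who were prescribed nothing.

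Under Usual care, residents with vision impairment are referred for an eye evaluation, so this arm is not cut off from spectacles or aids.

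**The concern.** A comparison between groups needs the same variable measured in the same way in both groups. Here one section names a two-arm test and another restricts the data to part of one arm. This is a mismatch between two explicit statements in the article, not a detail left to a fuller document: an analysis plan can choose the model, but it cannot analyse answers that nobody was asked to give.

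At stake is whether one secondary comparison can be reported at all. If the analyst reaches the end of the trial without usual-care records, any comparison would have to be built on an assumption about that arm. The ROC figure alone would describe use among people given a device, not the effect of offering the model of care.

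**Working it through.** The plan states no figure for the device-use comparison, so the check is a comparison of the sections, with arithmetic only for scale.

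**Step 1. Scale.** The Sample size section gives 76 × 3.5 = 266, then 266 / (0.90 × 0.75) = 394.07, stated as 395. The target reproduces, and the present point does not depend on it. With 1:1 allocation of facilities, and assuming similar numbers per arm, 395 / 2 = 197.5, so about 197 participants are in usual care. With the plan's 25% loss to follow-up, 395 × 0.75 / 2 = 148.1, so about 148 are still under follow-up.

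**Step 2. Who supplies data, as written.**

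| Group | Device-use questions described? |
|---|---|
| ROC, prescribed spectacles or aids | Yes |
| ROC, prescribed neither | No |
| Usual care, with or without a device | No |

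**Step 3. Can the tests be computed?** The Chi-squared table (used / not used by arm) has a usual-care column total of 0. Its expected counts are 0 and the statistic is undefined. The test of time in use has one sample instead of two.

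**Step 4. Could usual care be set to zero use?** Not from the documents. Usual-care residents are referred for evaluation, and the Sample size section expects some in that arm to seek vision care on their own. Their use is unknown, not zero by definition.

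**Step 5. Could imputation fill the gap?** The Missing data section names multiple imputation by chained equations. When a variable is absent for a whole arm, the arm effect on it cannot be estimated from the data. Any imputed usual-care value would come from the model fitted to ROC respondents plus an untestable assumption.

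**Step 6. Does the ROC side follow intention to treat?** Let π be the proportion of ROC participants prescribed a device, u the proportion using a device among them, and v the proportion using a device among the rest (for example, spectacles already owned). The intention-to-treat quantity for ROC is πu + (1 − π)v. The described data give only u. Because being prescribed a device happens after randomization, u has no randomized counterpart in usual care.

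**Step 7. Other possible sources for usual care.** Presenting acuity is measured in everyone with current correction, so an assessor could see whether spectacles are worn at the visit. That gives neither frequency nor duration of use. The Cost-effectiveness analysis section refers to vision services received by usual care; that is service use for costing, not device use.

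**The case against.** **The article is condensed.** The schedule figure and the full protocol are not shown, and the usual-care form might carry these questions. That is possible, but the text does not merely stay silent: it names the intervention arm as the respondents. If the full protocol differs, the article still needs correcting.

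**Some usual-care information exists.** A crude comparison of wearing or not wearing spectacles at the acuity test is not shown to be impossible. This stands, and it is why the point is limited to frequency and duration of use. It does not rescue the stated test of use time or any test covering low vision aids.

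**Three stronger readings are tempting.**

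- A reader might infer that the arm-specific question unmasks the assessors and so compromises the primary outcome. The Randomization section says: "The allocation sequence will be concealed from the research assistants enrolling and assessing participants". It leaves these assistants out of its list of unmasked roles ("Residential care facility staff, the research study coordinator, and the eye health professionals delivering ROC will not be masked to the group allocation"), and it adds: "Participants in the same aged care facility will all be assigned to the same study arm". One arm-specific question could therefore reveal a facility's arm to whoever asks it. But the text conceals the sequence and does not state outright that follow-up assessors are masked. It does not say who asks the device questions; an unmasked coordinator could. Study spectacles worn at the acuity test might reveal the arm in any case. The documents show a risk worth avoiding, not a breach.
- A reader might infer that absent usual-care answers will be counted as non-use, biasing the result towards ROC. That would be the direction if it were done, but nothing in the article says it will be.
- A reader might infer that the outcome listed in the Background ("rate of falls, and eye care utilization, compared to the usual care group at the two- and six-month visits") fails for the same reason. Eye care utilization more naturally means use of services, and the article describes use of visual devices separately. The two are not clearly the same endpoint.

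**Conclusion.** The two sections cannot both stand. As written, the between-arm tests of device use and use time have no described usual-care data on frequency or duration, and the ROC data come from a subset formed after randomization. The tests cannot validly be done.

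The size is 0 described records from about 197 usual-care participants at enrolment, or about 148 after the planned loss. Both counts assume similar numbers per arm. The conclusion itself needs no numerical assumption, only that the article's description of who is asked is accurate.

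The scope is one secondary comparison. The sample size and the primary vision outcome do not depend on it, and harm to assessor masking is not established.

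**What to change.** **Where follow-up visits remain.** Change Person-centered outcomes (secondary) so that every participant in both arms is asked the same questions at two and six months: which distance glasses, near glasses or low vision aids they have, and how often, for how long and for what tasks each is used. Having no device should be recorded explicitly and counted as no use. Compare over all randomized participants, not only those prescribed a device. If usual care is asked only from some date onward, state how many participants in each arm were asked and limit the comparison to visits at which both arms were asked.

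**Where usual-care visits have passed and the data were not collected.** Delete the between-arm device-use tests from Statistical analysis and report frequency, duration and tasks of use descriptively for ROC only, giving the number prescribed a device as the denominator.

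**Precaution in either case.** Put these questions after the acuity tests and interviews, or have staff who already know the allocation ask them.

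**Cost.** The first option adds a few questions to existing visits, plus the ethics review the article already foresees for protocol changes. Its reach is limited: recruitment began on 18 June 2014 and was due to end by 1 December 2018, days after publication on 26 November 2018. If baseline falls near recruitment, the last six-month visits would fall around 1 June 2019, so only late recruits could still be asked. The second option costs only a change of wording.
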